## 6. MORBIDITY

### Morbidity

| #  | Outcome Measures                                             | Control | Intervention | Delta |
|----|--------------------------------------------------------------|---------|--------------|-------|
| 2a | i. Any morbidity                                             |         |              |       |
|    | At or prior to discharge                                     | X       | X            | X     |
|    | Between discharge and 30 days                                | X       | X            | X     |
|    | Other                                                        | X       | X            | X     |
|    | Total                                                        | X       | X            | X     |
|    | At or prior to discharge
OR between discharge and 30 days | X       | X            | X     |
| 2b | ii. Morbidity by grade (I, II, IIIa, IIIb, IVa, IVb)         |         |              |       |
|    | at least one Grade I                                         | X       | X            | X     |
|    | .                                                            | X       | X            | X     |
|    | at least one Grade IVb                                       | X       | X            | X     |
|    | Other                                                        | X       | X            | X     |
|    | Total                                                        | X       | X            | X     |
| 2c | iii. Survival (grade V)                                      | X       | X            | X     |
| 2d | iv Morbidity by highest grade                                | X       | X            | X     |
| 2e | v. Number of people with no morbidity                        | X       | X            | X     |
| 2f | vi. Morbidity by type (eg arrhythmia, wound infection, etc)  |         |              |       |
|    | Type                                                         | X       | X            | X     |
|    | .                                                            | X       | X            | X     |
|    | Type                                                         | X       | X            | X     |
|    | Other                                                        | X       | X            | X     |
|    | Total                                                        | X       | X            | X     |

Note: the "other" categories are included for completeness and will be omitted if absent

Note: this is a list of patients, not complications. Because a patient can have more than one complication of different times/grades, an arm may not add to 100%. See appendices for worked examples

#### 6.1 i. Any morbidity

This secondary outcome is reported regardless of timepoint. The information to calculate it is derived from the morbidity grade as specified on the CRFs Complications Grading 1 and Complications Grading 2. It is a binary variable and collectively a count/rate (0-n/%). The entry is defined as the number of patients with at least one complication divided by the number of patients.

For worked examples of this please see the appendices.

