#### European Organisation for Research and Treatment of Cancer Quality of Life Questionnaire – Colorectal cancer module (EORTC-QLQ-CR29) – 10 mins

Widely used and validated CRC-specific HRQoL instrument assessing CRC-specific functional status and symptoms post-operatively.

Hospital Anxiety and Depression Scale (HADS) – 5 mins

Widely used and validated anxiety and depression questionnaire.

Resource use questionnaire – 5 mins

A modified Client Service Receipt Inventory [65] will be used to collect data on use of primary care services, social care services, and other health care professional, as well as time off work.

Concomitant medication (5 min)

Participants will be asked to bring their prescription or a list of their medication at the screening visit for these to be recorded.

Weight and body composition – 3 mins

Weight will be measured barefoot and with light clothing to the nearest 0.1kg using a calibrated digital scale which will also estimate body composition using bioelectrical impedance.

Height – 2 mins

Height without shoes will be measured to the nearest 0.1cm using a stadiometer.

5 times sit to stand test – 3 mins

Participants sit in a standard straight-backed stable chair (without wheels) positioned by a wall. They then stand fully and sit back down, without using the hands, five times, as quickly as possible.

Post-operative complications

Presence and type of any morbidity. This will be based on medical records for complications during the hospital stay and on participants reporting it using a standard proforma for complications following discharge. They will be graded (as I-V) independently by two researchers blinded to treatment allocation with the Clavien-Dindo classification of post-operative complications, the most widely used and validated measure.[66]

Table 1: Clavien-Dindo classification of post-operative complications

| Morbidity grade definition |                                                                                                                                                                                                                                                                                                                                                             |

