## **9.10. Early Discontinuation/Withdrawal of Participants**

During the course of the study a participant may choose to withdraw early from the intervention at any time. This may happen for several reasons, including but not limited to:

- The occurrence of what the participant perceives as an intolerable AE.
- Inability to comply with study procedures
- Participant decision

Participants in the care as usual group: They may opt out of study assessments but may remain on study follow-up.

Participants in the intervention group: They may stop the intervention and/or study assessments but may remain on study follow-up and will be encouraged to do so.

All participants may also withdraw their consent, meaning that they wish to withdraw from the study completely. In the case of withdrawal from both treatment (i.e., intervention) and active follow up, the following options for a tiered withdrawal from the study will be given to participants and explained in the participant information sheet.

According to the design of the study, option 1 below will be the default. Alternatively, participants can explicitly opt for option 2.

- 1) Participants may withdraw from active follow-up and further communication but allow the study team to continue to access their medical records and any relevant hospital data that is recorded as part of routine standard of care; i.e., CT-Scans, blood results and disease progression data etc.
- 2) Participants can withdraw from the study but permit data obtained up until the point of withdrawal to be retained for use in the study analysis. No further data would be collected after withdrawal.

In addition, the Investigator may discontinue a participant from the intervention at any time if the Investigator considers it necessary for any reason including, but not limited to:

- Participant declining surgery
- Pregnancy
- Ineligibility (either arising during the study or retrospectively having been overlooked at screening)
- Significant protocol deviation
- Significant non-adherence with the intervention or trial requirements
- Clinical decision

The follow-up of participants that have withdrawn from the intervention but not from active follow-up will continue with the standard follow-up assessments of the study.

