Data from randomised participants who undergo curative surgery for colorectal cancer will be analysed. Post-randomisation withdrawal from the study will not result in exclusion of the data for that participant from the analysis. However, participants will be replaced as per section 9.3 if

- they have been randomised but have not undergone curative surgery for colorectal cancer
- they have been randomised but deemed ineligible during the study or retrospectively  
or
- they have withdrawn before randomisation.

The type of withdrawal and reason for withdrawal will be recorded in the eCRF.

If the participant is withdrawn due to an AE, the investigator will arrange for frequent telephone calls as agreed with the participant until the AE has resolved or stabilised (also see sections 9.7, 10, and 13.3.2) and up to the point the participant completes the study. If a participant is withdrawn from treatment due to pregnancy the pregnancy will be followed-up to outcome. See the Safety Reporting section below.

The type of withdrawal and reason for withdrawal will be recorded in the eCRF.

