## 3. DEFINITION OF POPULATION FOR ANALYSIS

Main analysis: All randomised participants that underwent surgery will be included in the main analysis on an intention-to-treat basis (ITT) regardless of withdrawal or non-adherence. An intention-to-treat basis assigns all randomised participants to their originally allocated group, whether they received their allocated randomised treatment arm approach or not, or dropped out or not. Participants who had their surgery less than 20 days since randomisation will be included in this analysis.

Per-protocol analysis: We will also conduct an analysis on a per-protocol basis. A per-protocol basis includes only those randomised participants who met all eligibility criteria, had no major deviations from the study procedures, and adhered to their assigned interventions. For the intervention group, this includes the participants who achieved  $\geq 5\%$  weight loss from baseline to the day of surgery. For participants in the usual care group, this excludes those who lost  $\geq 5\%$  weight loss from baseline to the day of surgery. Participants who had their surgery less than 20 days since randomisation will not be included in this analysis.

Adverse events: The adverse event analysis will include the participants in the control group and the participants commencing the intervention in the intervention group.

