## 15. FURTHER CONSIDERATIONS ON THE ANALYTICAL APPROACH

### 15.1 Missing data

Missing data will be checked and either corrected if wrong or left if legitimate. Missing data will not be imputed (but see sensitivity analysis). The amount of missing data will be quantified and analyses for variables with missing data will be noted as such.

Mixed effects models usually do not require imputation as they are usually robust to missing data (although this depends if missing data is missing at random or not).

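### The morbidity rate has no rule for operated patients without a 30-day report; read literally, those with no in-hospital complication count as complication-free

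*Combined protocol and SAP*

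**What the plan says.** - **Ratio.** Supplement 6.1 on any morbidity: "The entry is defined as the number of patients with at least one complication divided by the number of patients". Supplement 6.2 uses the same denominator for each grade, and 6.5 (no morbidity) simply refers back to 6.1. The worked example in supplement 26.1 divides every row, including the one for discharge to 30 days, by all patients in the arm.
- **Population.** Supplement 3: "All randomised participants that underwent surgery will be included in the main analysis on an intention-to-treat basis (ITT) regardless of withdrawal or non-adherence". Protocol 9.10 agrees: "Post-randomisation withdrawal from the study will not result in exclusion of the data for that participant from the analysis".
- **Source of the data.** Protocol 9.6.4, under post-operative complications, says of any morbidity: "This will be based on medical records for complications during the hospital stay". After discharge it relies "on participants reporting it using a standard proforma for complications following discharge". Protocol 9.8 places this reporting at the post-operative assessment, with a window of 27 to 37 days. Under operative outcomes, 9.6.4 separately takes certain 30-day events from medical records: surgical site infection, stoma complications, anastomotic leaks, intensive care and high dependency time, re-operation and re-admission.
- **Withdrawal.** The default in protocol 9.10 is option 1: "Participants may withdraw from active follow-up and further communication but allow the study team to continue to access their medical records". Option 2, which must be chosen explicitly, ends all collection.
- **Missing data.** Supplement 15.1 says that missing values are not imputed, and that their amount is quantified and noted. Protocol 11.8 says that they are imputed as the SAP describes. SAP 6.3 covers the progression criteria only, SAP 6.4 plans no sensitivity analyses, and the list in supplement 15.4 has none for missing data.

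**The concern.** In-hospital complications are known for everyone operated on. Graded complications after discharge depend on a visit that some patients will not attend. The denominator does not change with attendance. A patient who left hospital without a complication and then missed the visit has unknown 30-day status, but nothing in the ratio separates that patient from one who attended and reported no problem.

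What is at stake is the usefulness of the morbidity estimate. Protocol 9.5 describes the nurses at the post-operative visit as assessors of the future primary outcome, so these rates may well inform the design of the definitive trial. A rate that falls as attendance falls would mislead that planning. If attendance differed by arm, it would also distort the between-group difference.

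**Working it through.** **No stated figure to reproduce.** The plan gives no expected rate or missing-data allowance for this outcome. Its nearest figures are in the worked example (supplement 26.1): with three patients per arm, the discharge-to-30-day row is 1/3 = 33% and 2/3 = 66%, so the denominator is indeed the whole arm. Every patient in that example has a recorded complication, so it does not show how an unseen patient is handled.

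**Inputs**
- p, true any-morbidity rate: 43% with obesity and 21% without (protocol 5). Using these rates for this trial's population is an assumption.
- d, proportion without a 30-day report: 15% at the green retention threshold (85%) and 34% at the lowest amber value (66%). This takes the retention criterion as attendance at the 30-day visit.
- f, share of affected patients whose only complication came after discharge: not in the documents; assumed 10% to 50%.
- Loss is assumed unrelated to outcome, with no back-up from records.

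**Post-discharge row.** Reported rate = true rate × (1 − d). The relative understatement is d: 15% or 34%.

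**Any morbidity.** A patient with an in-hospital complication is already in the numerator, so only the share f is exposed. Reported rate = p × (1 − f × d), and the understatement is p × f × d.

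| p | d | f = 10% | f = 30% | f = 50% |
|---|---|---|---|---|
| 43% | 15% | 0.6 points | 1.9 points | 3.2 points |
| 43% | 34% | 1.5 points | 4.4 points | 7.3 points |

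For example, 0.43 × 0.50 × 0.34 = 0.0731. In an arm of 36 the range is 36 × 0.00645 = 0.2 to 36 × 0.0731 = 2.6 patients. At p = 21% it runs from 0.21 × 0.10 × 0.15 = 0.3 points to 0.21 × 0.50 × 0.34 = 3.6 points.

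**Between arms.** With equal rates, the false difference is p × f × (difference in d). Equal loss gives zero. An assumed loss of 25% in the intervention arm and 5% in control gives 0.43 × f × 0.20, which is 0.9 to 4.3 points in favour of the intervention for f from 10% to 50%.

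**Bounds.** At p = 43% and f = 30%, the literal ratio gives 41.1% (15% loss) or 38.6% (34% loss). Counting every unknown as an event adds d × (1 − p × (1 − f)):
- 41.1% + 0.15 × 0.699 = 51.6%
- 38.6% + 0.34 × 0.699 = 62.4%

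**The case against.** The strongest reply is that the plan never says an unseen patient is complication-free. Supplement 15.1 could be read to make unknown status missing, to be counted and noted. That is a fair reading, so a reader who infers a written rule of coding missing as none, or an outright contradiction between 6.1 and 15.1, goes further than the text. But 15.1 does not say which denominator to use once data are missing, and protocol 11.8 points the other way. The two readings give different rates.

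A reader might also infer that post-discharge complications can be known only from self-report. The documents do not support this. Protocol 9.6.4 takes several 30-day events from records, 11.11 uses hospital records for secondary care including complications, 13.2 has missing data chased with telephone contact where appropriate, and default withdrawal keeps access to records. The loss is therefore partial. Even so, no section requires a records search to day 30 to supply graded morbidity for a non-attender. Supplement 8.4 and 8.6 derive infection and leaks from a complications form fed by earlier forms such as the discharge form.

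Third, the outcome is secondary and descriptive, no p-values are reported, and morbidity is not a progression criterion. Sampling error is also large. Suppose a true post-discharge rate of 20% in both arms, with 30% of the intervention arm and 10% of control not seen. The reported rates are 0.20 × 0.70 = 14% and 0.20 × 0.90 = 18%, a difference of 4 points. The 95% half-width at 36 per arm is 1.96 × √(0.14 × 0.86/36 + 0.18 × 0.82/36), or about 17 points. This limits the consequences here, but a bias of this kind does not shrink with sample size if the definition is reused in the definitive trial.

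Finally, SAP 1 refers to a separate data definitions and tables document, which was not available for this review and may contain a rule.

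**Conclusion.** The gap is real but limited. The documents at hand do not say how to treat an operated patient with no in-hospital complication and no 30-day report. Taken literally, the ratio makes that patient a non-event and adds them to the no-morbidity count.

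The relative understatement of 15% to 34% belongs to the post-discharge row alone. It should not be carried over to any morbidity, where the corresponding figures are about 0.6 to 3.2 points at 15% loss and 1.5 to 7.3 points at 34%, from a true 43%. All of these assume no help from records and loss unrelated to outcome; the any-morbidity figures also rest on the assumed 10% to 50% share with post-discharge complications only. Record back-up would make them smaller. Loss related to complications could move them either way, and the documents give no basis for saying which.

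A reader might infer that the rule manufactures a treatment benefit. It does so only if loss differs between arms, and nothing in the plan shows that it will. The progression decision is not affected. The change is still worth making because it improves both the source and the denominator of the estimate, at little cost. Supplement 9.2 already applies the same logic to days alive and out of hospital, where local teams are to confirm that the patient is alive at day 30.

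**What to change.** 1. In protocol 9.6.4 and supplement 6.1 to 6.6: for any participant without a completed 30-day proforma, extract complications from discharge to day 30 from hospital records where consent allows (default option 1). Use the same blinded grading and flag the data source.
2. Where neither source exists and there was no in-hospital complication, class the patient as unknown. Report the number with known status per arm. Give bounds for any morbidity, and for its complement no morbidity, with all unknowns counted as none and then as events.
3. Keep every patient with a documented in-hospital complication in both of those outcomes as having morbidity, since their status is known. Use the known-status denominator only for the row covering discharge to 30 days.
4. Reconcile protocol 11.8 (impute) with supplement 15.1 (do not impute) for the secondary outcomes. If the data definitions document already holds a rule, refer to it in supplement 6.

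The cost is a few sentences, one extra table line and a records check for non-attenders. The drawback is that hospital records may miss minor events treated in primary care, so the two sources are not equivalent; flagging the source lets the reader see this.

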#### 6.2 ii. Morbidity by grade (I, II, IIIa, IIIb, IVa, IVb)

This secondary outcome is reported by grade regardless of timepoint (i.e., a complication can occur at either discharge or 30-days follow-up). The information to calculate it is derived from the morbidity grade as specified on the CRFs Complications Grading 1 and Complications Grading 2. The entry for each grade X is defined as the number of patients with at least one complication of grade X divided by the number of patients. It is a categorical variable. Each category is a count/rate (0-n/%) and will be modelled as a binary variable.

For worked examples of this please see the appendices.

### 6.3 iii. Survival (grade V)

This secondary outcome is reported for a single grade regardless of timepoint. The information to calculate it is derived from the morbidity grade as specified on the CRFs Complications Grading 1 and Complications Grading 2. It is a binary variable and collectively a count/rate (0-n/%). Given the expected low count, it is unlikely that this will be analysed statistically.

### 6.4 iv Morbidity by highest grade

As ii above. This secondary outcome is reported for a single grade regardless of timepoint. If a participant has one coded complication, the grade of that complication will count as the highest graded morbidity. If a participant has at least two complications, the highest grade will be counted for this variable. It is a categorical variable & each category is a count/rate (0-n/%). Each category will be modelled as a binary variable.

For worked examples of this please see the appendices.

### 6.5 v. Number of people with no morbidity

As i above.

### 6.6 vi. Morbidity by type (eg arrhythmia, wound infection, etc)

This secondary outcome is reported regardless of timepoint. The information to calculate it is derived from the complication type as specified on the CRFs Complications Grading 1 and Complications Grading 2 (as derived from previous CRFs eg Hospital Stay and Discharge). It is a categorical variable & each category is a count/rate (0-n/%). Each category will be modelled as a binary variable.

## 7. ONCOLOGICAL OUTCOMES

### Oncological Outcomes

| #  | Outcome Measures                  | Control | Intervention | Delta |
|----|-----------------------------------|---------|--------------|-------|
| 3a | iv. Resection margins             | X       | X            | X     |
| 3b | v. Recurrence                     | X       | X            | X     |
| 3c | vi. New primary/ secondary cancer | X       | X            | X     |

#### 7.1 iv. Resection margins

This secondary outcome is reported at discharge. The information to calculate it is derived from the resection margins as recorded on the CRF Hospital Stay and Discharge. It is recorded as a continuous variable and a measurement of distance. It will be reduced to a binary measure (involved/not involved) and collectively a count/rate (0-n/%).

#### 7.2 v. Recurrence

This secondary outcome is reported at 3 years. The information to calculate it is derived from the recurrence or metastatic type data on the CRF NBOCA. It is a binary variable and collectively a

count/rate (0-n/%). Due to low expected numbers, we do not plan an analysis for this. It will be depicted using survival curves.

